**Form FHS015: Research Protocol - Section C**

Title: Autism Caregiver Coaching in Africa

1. **BACKGROUND**

Globally there is growing recognition of the importance of strengthening the capacity of caregivers and providers to *implement community-based services that support improvements in quality of life of autistic people*.^1^ Early autism intervention is recognized as critical because when delivered by specialist interventionists it can significantly improve child and family outcomes, reduce the need for services at a later age, and be a cost-effective approach.^2, 3^ Most autistic people live in LMIC, where systems of care do not provide developmental screening or early intervention.^4, 5^ By 2050 forty percent of the world’s children will live in Africa.^8^ This demographic shift highlights the importance of *developing feasible early intervention services that can be scaled-up in existing systems of care*. Consistent with Global Brain FOA priorities and NIMH Strategic Objective 4, there is an urgent need to develop autism services that foster high quality equitable care.

[figure not shown]
Research has demonstrated that caregivers can be coached to deliver early intervention strategies during everyday activities with their young autistic child.^10^ Low intensity caregiver coaching can impact caregiver-child interaction styles and improve child developmental outcomes.^23, 24^ **N**aturalistic **D**evelopmental **B**ehavioral **I**nterventions (**NDBI**) comprise a class of early intervention approaches that have been effectively delivered by caregivers.^11^ The Early Start Denver Model (ESDM) is an evidence-based NDBI.^12^ In the ESDM approach, strategies increase a child’s attention and engagement with their caregiver, thereby increasing opportunities for learning social and communication skills, leading to improvements in developmental outcomes (See Figure 1).

The efficacy of ESDM delivered via therapists, caregivers, and teachers has been evaluated in a wide range of cultures, including in Israel, France, Taiwan, Italy, China, and Japan, among others.^25-33^ Recent meta-analyses indicate that ESDM is efficacious for improving social, language, and cognitive skills.^34, 35^ A recent systematic review of caregiver-delivered social communication interventions for young autistic children concluded that ESDM qualified as an established evidence-based practice.^10^ While these studies indicate that caregiver-coaching based on ESDM has promise for addressing the needs of LMIC, the proposed research aims to address three important gaps in the existing literature. First, very few studies to date have included *diverse stakeholders*, including autistic self-advocates, in the research process.^36^ Such involvement is important for ensuring that the intervention is acceptable to the autism community.^37^ Second, caregiver coaches in most studies to date *have been highly trained specialists,* usually licensed in the fields of psychology and/or education*.* Lack of access to such specialists in most parts of the world requires that studies include task shifting to non-specialists as an implementation strategy. Third, in a meta-analysis of non-specialist delivered autism intervention, only two studies included participants from LMIC.^38-40^ Furthermore, in these two studies ‘non-specialists’ were certified teachers and therapists, a workforce unlikely to be scalable in Africa. In a study conducted in India, lay health workers under specialist supervision delivered 12 coaching sessions of a developmental intervention, demonstrating positive effects on children’s outcomes.^41^ This study provides preliminary evidence of the feasibility of non-specialist delivered early autism intervention in India, but implementation determinants will be different in other regions of the world, such as Africa. *Thus, our goal is to develop a feasible, scalable early autism intervention model in Africa by conducting research with culturally and linguistically diverse participants in community-based settings, that is inclusive of diverse stakeholder perspectives and incorporates task-shifting.*

In Africa, community health workers are often proposed as the non-specialists to target for task-shifting.^42^ In some LMIC, early childhood development services have been integrated into maternal and child community health worker programs.^43, 44^ *Challenges* with this approach include: limited community health worker training in early child development; difficulties managing competing demands resulting in poor quality of care and burn out; and lack of individualization of approach.^45-47^ This lack of individualization is particularly problematic for children with variable developmental profiles, which is seen in autism. *In the current proposal, we aim to address each of these challenges* by working with non-specialists trained in early child development, with dedicated time to coach, who work under supervision, and use an intervention that can be tailored to meet individual needs. Addressing these challenges will help create a non-specialist workforce that is well-positioned to deliver early autism intervention, thereby increasing the likelihood of long-term sustainability and scalability of the approach.

**Foundation for Proposed Project Built with NIMH R21 Funding**

*In South Africa few families with young children are able to access early autism intervention due to limited services and structural barriers*.^13, 14^ Those able to access services receive one 30-minute therapy session every 4–6 weeks. Caregivers are not included in sessions and typically asked to wait outside the room. Poverty and the legacy of apartheid remain significant structural barriers.^22^ Racial variation in expressive language has been documented in a neurodevelopmental clinic, with a significantly greater number of Black compared to White children non-verbal at diagnosis (94% vs 42%).^48^ The need for early autism intervention is increasing, with a documented 276% rise in the number of children on the waiting list for special education services.^49^

*Implementation context is critical to consider in early autism intervention*, particularly the ‘fit’ between intervention and context. Implementation frameworks specify the complex context for evidence-based practice implementation. The *Exploration, Preparation, Implementation, Sustainment (EPIS) framework* has been used to examine evidence-based practice implementation in publicly funded services.^21, 50^ EPIS highlights influential contextual factors within 4 phases: Exploration, Preparation, Implementation, and Sustainment and factors that hinder or support the implementation process when selecting, using, and sustaining evidence-based practice.

*A partnership between Duke University and the University of Cape Town (UCT) has laid the groundwork for an innovative and scalable coaching intervention.* The following achievements provide a strong foundation for our proposed project.

[figure not shown]
First, we identified Early Childhood Development (ECD) practitioners as the *non-specialist workforce* that could deliver the intervention.^14^ A partnership between this workforce and the National Education Department has been established.^19^ ECD practitioners are well-suited for this role as they are employed by the Education Department, trained in early child development, supervised, and supported by national policy.^51^ Alignment of the ECD workforce and Education Department at a national level is important for future scale-up. Second, we *identified the NDBI approach* based on local interest and available resources. Third, we evaluated the ‘*fit’ of NDBI-caregiver coaching with South African dyads*.^13, 15, 17^ We conducted interviews with caregivers and behavioral coding of caregiver-child interactions to understand interaction styles, and common daily routines in which intervention could be carried out. Fourth, we systematically *adapted ESDM procedures for effective delivery by non-specialists*. Fifth, we conducted a pilot study to *demonstrate that caregivers can learn NDBI strategies* when coached by ECD practitioners and that growth in child social communication occurs.^52^ Finally, mindful of the ‘digital divide’, intervention *materials were adapted to be shared through WhatsApp*, a low-cost messaging software.^18^ These achievements are shown in **Figure 2**.

1. **PURPOSE OF THE STUDY**

We now propose to build on this foundation by conducting a *type 1 hybrid effectiveness implementation trial of the intervention, delivered by non-specialists, within an existing system of care in South Africa*. The *main objectives* of this project are as follows:

**Aim 1**: Evaluate the effectiveness of an NDBI caregiver coaching intervention delivered by non-specialists relative to usual care for improving developmental outcomes for young autistic children in South Africa and assess the cost-effectiveness of this approach;

**Aim 2**: Identify the determinants (barriers and facilitators) that impact successful implementation of NDBI caregiver coaching delivered by non-specialists in South Africa; and

**Aim 3**: Build r**esearch capacity.** We aim to accelerate autism research capacity building in South Africa and extend it to Tanzania, through a tailored and systematic program of research training. Early career researchers at the University of Cape Town in South Africa, and Kilimanjaro Christian Medical Center in Tanzania will receive research training and be integrated into ongoing study activities. This aim will build sustainable autism research capacity and establish an African autism research network. We plan to build on our current relationships with families, practitioners, and policy makers by formalizing these relationships and including other key stakeholder groups such as South African autistic self-advocates through a *community-academic partnership, a key bridging factor in the EPIS implementation framework*.^21^

*This project also offers a unique opportunity to study variability in autism-related behaviors*. Exploratory components of Aim 1 will assess the degree to which response to intervention is moderated by dimensional child characteristics. In addition, using an innovative digital assessment method, changes in dimensional autism-related behaviors will be examined. Finally, cross-cultural differences in dimensional autism-related behaviors will be evaluated via comparison with existing quantitative phenotypic data gathered in U.S. studies conducted by the PI and co-investigators using the same measures.

1. **METHODOLOGY**
   1. **Study Design**

**Community-academic partnership.** In the proposed project, we will expand upon our work by conducting a *type 1 hybrid effectiveness implementation trial of caregiver coaching, delivered by non-specialists, within an existing system of care in South Africa*. With the hybrid type 1 design our primary objective is to determine the effectiveness of the coaching intervention, and our secondary objective is to identify implementation determinants for scale-up. To date, stakeholders have been integral to our work and engaged through public forums and research activities. We now plan to formalize these relationships through a community-academic partnership. *A community-academic partnership fits within EPIS as a bridging factor that can address potential ideological differences, help ensure research products are acceptable to end-users, and support longitudinal stakeholder engagement across the research cycle*.^21, 73^ The PI has extensive experience with forming such partnerships. At Duke, she currently directs the Duke Autism Center of Excellence Dissemination and Outreach Core, which includes a Community Engagement Advisory Board. This board is racially/ethnically diverse and includes autistic self-advocates, parents, educators, healthcare providers, and business leaders. This experience will be useful in designing and sustaining the community-academic partnership in the proposed project. [name], an implementation scientist and expert in autism research is a consultant on the proposed project and will advise on the formation and measurement of partnership functioning.^74^ The Partnership will be comprised of the PI, Co-PI, the Education Department Director and the Deputy Chief of Inclusive and Specialized Education Support, and 12 stakeholders (caregivers, autistic adults, ECD practitioners, and school supervisors). We will ensure that the cultural and linguistic diversity of South Africa is represented within this partnership. Participation will include 4-5 meetings annually. Members will receive an honorarium for attending each meeting. Meetings will last 2-4 hours. Agenda items will vary by project stage and include: (1) Coaching materials and approach; (2) Assessments, including qualitative interviews; (3) Interpretation of findings; (4) Community dissemination messages and avenues; (5) Identifying what the research team should leave behind for the community; and (6) Emerging topics of interest. To ensure stakeholders, particularly autistic self-advocates and caregivers, feel they are authentic partners, we will offer pre-meetings to set the context, encourage participation, and provide strategies to facilitate discussion.

**Aim 1: Effectiveness trial evaluating the intervention model**

**Overview of intervention trial design and arm allocation.** *The goal of the intervention trial is to evaluate the effectiveness of NDBI caregiver coaching delivered by non-specialists relative to usual care for improving developmental outcomes for young autistic children in South Africa and assess the cost-effectiveness of this approach*.

[figure not shown]
The study design will be an individually randomized group treatment RCT with a delayed treatment control group (**Figure 8**). 150 children, ages 18-72 months, with a DSM-5 diagnosis of autism spectrum disorder (ASD) and their caregivers will be recruited on a rolling basis, with arm allocation (coaching vs. delayed treatment control) conducted using a minimization approach with child sex balanced across groups.^75^ The intervention will be offered to the delayed treatment control group immediately after follow-up assessment (6-months after baseline). Offering the intervention to both groups is of ethical importance in an environment with few services and will enhance retention. Once control dyads have completed the intervention, the degree to which the trend in the control group is consistent with any treatment effect detected in the main trial comparison will be assessed.

Primary outcomes will be distal measures of communication abilities, as assessed by the VABS-3 - Communication Domain Standard Score and the Griffiths III - Language and Communication Developmental Quotient.^70, 71^ Key secondary outcomes will include proximal measures of the quality of the caregiver-child interaction which will be coded using the JERI coding scheme.^67, 68^ *Three dimensional measures that all assess level of autism symptom will be included*: the Social Responsiveness Scale-2 (SRS-2), the Childhood Autism Rating Scale, Second Edition (CARS2), and the S2K digital assessment tool.^58, 76, 77^

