**Characteristics of the study population**

**Aim 1.** As we did previously with the R21, caregiver-child dyads will be recruited from school wait lists. Aim 1 inclusion criteria are: (1) child’s age is 18-72 months, (2) child meets DSM-5 criteria for ASD, informed by Autism Diagnostic Observation Schedule, Second Edition (ADOS-2) (*Note: DSM-5 is the primary diagnostic framework utilized in South Africa. The feasibility of the ADOS-2 in Afrikaans and Zulu, two high-frequency languages in South Africa, has been established*),^78, 79^ (3) child’s caregiver speaks isiXhosa, isiZulu, Afrikaans, or English (97% of Western Cape languages), (4) child’s race is African or Coloured (South African term for mixed race), (5) lives in recruitment area, and (6) caregiver is ≥18 years. Exclusion criteria are: (1) genetic disorder of known etiology (e.g., fragile X syndrome), (2) significant sensory or motor impairment that would preclude use of the play materials, (3) major physical abnormalities that would interfere with participation in the intervention, a (4) history of serious head injury and/or neurological disease, and (5) caregiver indicates they will be unable to attend assessments and 12 sessions. We will enrol 150 caregiver-child dyads in Aim 1 (300 participants).

**Aim 2.** Participants will include: (1) *those involved in intervention implementation through participation in the intervention trial; and (2) community-academic partnership members*. Specifically, caregivers who receive NDBI coaching, ECD practitioners who conduct coaching, the Education Department autism outreach team who supervise ECD practitioners, and Education Department leadership will be included. These participants will be directly involved in intervention implementation and be able to provide input on the specific outer and inner contextual, and innovation factors outlined in the EPIS framework**.** Community-academic partnership members include the PI, Co-PI, Education Department leadership, and other stakeholders (for e.g., caregivers and autistic adults). These participants will provide input on functioning of the community-academic partnership, a key bridging factor in EPIS. Education Department leadership, specifically the Director and Deputy Chief of Inclusive and Specialized Education Support will be in both participant groups. We will enrol 20 participants for Aim 2.

- 1. **Recruitment and Enrolment**

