**Recruitment plan.** The proposed project will utilize the same recruitment procedures (for Aim 1 participants) that were utilized in the Global Brain R21, with caregiver-child dyads being recruited from school wait lists. Eligible children with autism within the study age range of 18-72 months will be identified by partner schools (Western Cape Education Department Schools: Mary Harding, Lentegeur, Beacon, and Glenbridge). Partner sites have records of children with autism, who have received a clinical diagnosis, and are waiting for public sector special education services. Across the four recruitment sites, 217 autistic children would likely be eligible to be recruited for initial screening, based on autism diagnosis and age. We plan to recruit 120 caregiver-child dyads in total. Based on experience from ongoing R21 activities we anticipate that at minimum 70% of these eligible subjects will meet full inclusion/exclusion criteria. This will most likely be related to caregiver availability to attend all intervention/assessment sessions. An exclusion criterion is a caregiver-child dyad that is unable to attend baseline and follow up assessments, as well as 12, 1-hour, caregiver coaching sessions. In order to account for the estimated 20% attrition, and ensure a final total sample size of 120 caregiver-child dyads, 150 caregiver-child dyads will initially be recruited. Enrolment will occur over a 39-month period beginning in month 5. Families will be invited to participate in the study by school staff using IRB approved recruitment materials. Those who are interested will be contacted by a research team member who will explain the study and gather the screener questionnaire data. If the child and caregiver meet checklist criteria and caregiver provides telephonic informed consent, the child and family will be enrolled. Data from the child, the caregiver-child dyad, and the caregiver are relevant to the study questions. Therefore, the parent/legal guardian will sign consent both on behalf of their young child with autism, and themselves. The caregivers and their children are recruited as a ‘unit’. Following screening consent, the Project Coordinator, in addition to screening the autistic child with for most inclusion and exclusion criteria, will conduct an additional screening of the caregiver. As part of the baseline assessment an ADOS-2 will be administered to inform DSM 5 autism spectrum disorder diagnosis. Participants will be informed throughout the recruitment process and study sessions that participation is voluntary and that they may refuse to answer any question for any reason. In addition, the caregivers of their child may refuse to participate or withdraw from the study at any time without penalty or loss of benefits to which they are otherwise entitled. In cases where a dyad requests change in caregiver due to change in personal circumstances negatively impacting their ability to attend sessions or assessments we will work with the family to identify and consent a caregiver that meets inclusion criteria.

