
Aim 2 participants will be purposively sampled and include (1) those involved in intervention implementation through participation in the intervention trial; and (2) community-academic partnership members. Specifically, multilevel stakeholders who receive (caregivers in the intervention arm), deliver (ECD practitioners), supervise (Education Department autism outreach team) NDBI coaching across 4 school partner sites. Furthermore, because the Education Department is our implementation partner, Education Department leadership will be included as participants. Community-academic partnership members include the PI, Co-PI, Education Department leadership, and other stakeholders (for e.g., caregivers and autistic adults).

**Retention strategies.** In the intervention study, based on our experience in R21, we estimate 20% attrition. Thus, 150 caregiver-child dyads will be recruited. Using strategies established during the R21 we will create a tracking log to document the dates of study visits, including intervention sessions and assessments, as well as other notes related to participant attendance and retention. A centralized tracking log keeps all study staff at UCT and Duke up-to-date and allows for the Project Coordinator and interventionists to track when visits are scheduled and make reminder calls in a timely manner. The tracking log also allows for study staff to document notes about participant circumstances that may influence scheduling (e.g., vacation dates, work schedules), note reasons for missed study visits, and record staff attempts to contact participants. These details all help inform individualized strategies to retain participants.

- 1. **Research Procedures and Data Collection Methods**

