**Data Analysis – Aim 1.** For the *primary objective*, co-primary outcomes include the VABS-3 Communication Domain Standard Score and the Griffiths III Language and Communication Developmental Quotient. For each outcome, an Analysis of Covariance (ANCOVA) type model will test for the effect of NDBI coaching at month 6 compared with usual care, adjusted for baseline differences between child intellectual ability as assessed by the Griffiths III Foundations of Learning Subscale with random effects to account for the partially nested design and for correlation within children over time. The Foundations of Learning Subscale assesses attention, memory, and processing speed. In addition, we will track all non-study intervention services and adjust the model for number of service hours received. The primary analysis will simultaneously model data from baseline, post-intervention, and follow-up assessments, before the delayed treatment control receives intervention. Once control dyads have completed the intervention, we will conduct additional analyses to assess the degree to which the trend in the control group is consistent with any treatment effect in the main trial comparison. For the *secondary objective*, each outcome will be analyzed separately using an ANCOVA model using the same form as for each of the primary outcomes. For the *tertiary objective* a mediation analysis will be performed using 4-month uptake in caregiver strategies as a mediator on the pathway between the intervention and 6-month co-primary distal outcomes.^84^ For the *1^st^ exploratory component*, each potential moderator will be considered separately by adding the following fixed effect terms to each ANCOVA model for each of the two primary outcomes: the potential moderator and its interaction with the NDBI treatment indicator. Qualitative interviews will be analyzed using an iterative coding and review process informed by grounded theory.^85^ For the *2^nd^ exploratory component*, changes in S2K dimensional quantitative measures of autism-related behaviors will be evaluated longitudinally (change over time) through data visualization (e.g. scatterplots) and group comparisons using a two-tailed Mann-Whitney U test. For the *3^rd^ exploratory component*, that includes cross-cultural comparison, visualizations and the Mann-Whitney U test will be used to compare the distribution of autism-related behaviors between the US and South African samples. For our primary analysis, our power calculations follow the approach of Moerbeek & Teernestra for an individually randomized group treatment design with clustering in one treatment arm^71^. Assuming 20% attrition in both arms, for 80% power and an alpha of 0.025, we need to enroll 75 dyads in the intervention and 75 in the control arm, for a total sample size of 150. For additional details see Human Subjects Section: Statistical Design and Power.

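### Child sex is the only minimisation factor named in a four-school trial, and the primary model names no school, age or sex term; adding school (and age band) would buy balance and a little precision

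*Protocol*

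**What the plan says.** Under Aim 1: Effectiveness trial evaluating the intervention model, the Protocol describes an "individually randomized group treatment RCT with a delayed treatment control group", with allocation "conducted using a minimization approach with child sex balanced across groups". Child sex is the only balancing factor named there or elsewhere in the text. Children may be 18 to 72 months old at entry.

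Under Characteristics of the study population, "caregiver-child dyads will be recruited from school wait lists". The recruitment plan (Recruitment and Enrolment) names four partner schools: "Across the four recruitment sites, 217 autistic children would likely be eligible to be recruited for initial screening". The split of these children by school is not given. In the same section, the Aim 2 sampling paragraph refers to people who receive, deliver or supervise "NDBI coaching across 4 school partner sites".

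Data Analysis – Aim 1 gives the size as follows: "we need to enroll 75 dyads in the intervention and 75 in the control arm, for a total sample size of 150". The primary model adjusts for the Griffiths III Foundations of Learning subscale and for hours of non-study services. Its random effects cover partial nesting and repeated measures within child. School, age and sex are not listed.

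**The concern.** Minimisation can balance several factors at once, so naming one leaves most of its value unused. School is the obvious omission. It is the route into the trial and a place of coaching, and the Aim 2 text treats school leadership and internal school support as influences on delivery. Age is a second candidate, given a 54-month entry range in a trial of language outcomes.

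The listed model does not make up for this. It contains neither omitted factor, and it also leaves out sex, the one factor that is minimised. If a factor is balanced by design but absent from the model, the standard error does not credit the balance achieved.

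At stake are a modest amount of precision in the month-6 comparison and the credibility of a baseline table in which one school may look lopsided.

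**Working it through.** **The plan's own figure.** Completers divided by (1 − attrition): 120 / (1 − 0.20) = 150, and 60 / 0.80 = 75 per arm. Both match the Protocol. The 80% power step cannot be reproduced, because the effect size, SD, intraclass correlation (ICC) and cluster size are not in this document.

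**Inputs.** From the Protocol: n = 150, 1:1 allocation, four schools, ages 18-72 months, sex minimised. Assumed, because the Protocol does not give them: 80% boys; ages uniform over the range (SD 54/√12 = 15.6 months); schools either equal or split 40/30/20/10%; the balancing arm chosen with probability 0.8 or 1.0.

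**Simulated imbalance.** There were 3,000 trials per setting, so the simulation error of a percentage is at most √(0.25/3000) = 0.9 points. Sex-only minimisation is compared with sex + school + three 18-month age bands. The split columns give the chance that at least one school is split that unevenly or worse.

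| Schools | Coin | Factors | 60:40 | 65:35 | 70:30 | Age gap, median / 95th percentile (months) |
|---|---|---|---|---|---|---|
| Equal | 0.8 | Sex | 46.1% | 14.4% | 2.6% | 1.72 / 5.04 |
| Equal | 0.8 | All three | 0.3% | 0.0% | 0.0% | 0.70 / 2.06 |
| Equal | 1.0 | Sex | 43.6% | 11.6% | 2.1% | 1.71 / 4.91 |
| Equal | 1.0 | All three | 0.0% | 0.0% | 0.0% | 0.64 / 1.85 |
| 40/30/20/10 | 0.8 | Sex | 57.6% | 30.6% | 13.1% | 1.69 / 4.92 |
| 40/30/20/10 | 0.8 | All three | 6.9% | 2.0% | 0.5% | 0.72 / 2.12 |
| 40/30/20/10 | 1.0 | Sex | 57.0% | 30.2% | 13.3% | 1.72 / 4.93 |
| 40/30/20/10 | 1.0 | All three | 0.8% | 0.2% | 0.0% | 0.65 / 1.79 |

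Under sex only, the largest within-school difference between arms had a median of 7 children and a 95th percentile of 13. With all three factors these were 1-2 and 2-4. The chance that the arms differ in mean age by more than 0.25 SD fell from 12-13% to about zero. The higher percentages for unequal schools come with a smallest school of about 0.10 × 150 = 15 dyads, where 9 against 6 is already 60:40.

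**Effect on the treatment comparison, in outcome SDs.**
- School: the SD of the chance contribution is √(ICC × E[Σd²]), where d is the difference between arms in a school's share of dyads. For equal schools, E[Σd²] ≈ 4 × 0.25 × 0.75 × 4/150 = 0.02. An assumed ICC of 0.02 gives √0.0004 = 0.020, and 0.10 gives √0.002 = 0.045. The simulations agree (0.020 and 0.045).
- Age: for an assumed age-outcome correlation r, the SD is r × √(4/150) = 0.163r, which is 0.016 at r = 0.1 and 0.049 at r = 0.3.
- For comparison, the standard error with 60 per arm, ignoring clustering and covariates, is √(2/60) = 0.183. The school and age figures use all 150; on 120 completers they rise by √(150/120) = 1.12, to at most about 0.055.

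**Power.** Take a nominal 80% at a two-sided 0.025 (the Protocol does not state sidedness). The standardised effect is then 2.241 + 0.842 = 3.083. Removing a variance share v gives power Φ(3.083/√(1 − v) − 2.241).
- School, v = ICC: 0.02 gives 80.9%; 0.10 gives 84.3%.
- Age, v = r²: r = 0.1 gives 80.4%; r = 0.3 gives 83.9%.

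Each source is taken on its own.

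**The case against.** **Sex may not be the only factor.** The text does not say that it is, the design figure is not shown, and a randomisation plan or SAP may list more. This stands as a limit on the finding, which concerns what the Protocol names. But allocation factors must be fixed before the first dyad is allocated. A later SAP can add covariates and recover much of the precision; it cannot restore balance.

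**Nothing stated is wrong.** This also stands. Individual allocation balanced on sex is valid, and chance imbalance on other factors is ordinary sampling variation.

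**Age matters less than the range suggests.** The co-primary outcomes are a standard score and a developmental quotient, both scaled relative to age, and the model uses baseline data and Foundations of Learning. This is accepted, and it makes age the lesser point. The key proximal outcome, a sum of JERI items, is not described as age-normed, so age keeps some relevance there.

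**Differences in local usual care are partly handled.** The model adjusts for non-study service hours. That covers part of what differs between schools, not all of it.

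A reader might infer three stronger claims, which the documents do not support:
- That the arms will be badly unbalanced. With equal schools of about 37 dyads, a 60:40 split is roughly 22 against 15, and 70:30 is uncommon.
- That school confounds the coaching effect. Randomisation is by dyad, so any imbalance is due to chance.
- That sex-only minimisation loads coaches unevenly or prevents coach and school differences from being separated. The Protocol does not say how many coaches there are or how they are assigned. If coaches are school-based, they are nested in school whatever the minimisation factors.

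**Conclusion.** The point holds as a moderate design improvement, with school the stronger half. Under sex-only minimisation, some school is split 60:40 or worse in about half of simulated trials (44-58%); with school and age band added this falls to 0-7%, with N unchanged. The cost of leaving the plan as it is consists of a few points of power at most, plus face validity. It is not bias or a type I error problem.

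The sizes rest on the assumed school shares, sex ratio, age distribution, coin probability, school ICC (0.02-0.10) and age-outcome correlation (0.1-0.3). The direction does not depend on them.

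**What to change.** In the Aim 1 allocation paragraph, name school (four levels) and, as a lesser point, child age band as minimisation factors alongside child sex, and state that a random element is kept. The simulations used three 18-month bands and, in one setting, a 0.8 probability of the balancing arm. If a randomisation plan already lists these factors, the Protocol should say so.

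In Data Analysis – Aim 1, include the minimisation factors as fixed terms in the primary and secondary models. If allocation has already begun, this part can still be done.

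The cost is small. Minimisation is already planned and no extra dyads are needed. School and age must be entered before allocation; the referring school supplies the first and screening the second. The models carry a few more fixed terms: with three age bands, 3 for school, 2 for age and 1 for sex, against an expected 120 completers.
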